#### Clinical outcomes

Static postural control and limits of stability (LOS) will be assessed using the AMTI Accugait Optimized™ force platform (AMTI, Inc., Newton, MA). The Accugait measures the three-dimensional applied forces (Fx, Fy, Fz) and moments (Mx, My, Mz) involved in balance and uses established algorithms to compute the location of the center of pressure (COP) and its associated variables with acquisition frequency set to 100 Hz. Data will be acquired, recorded, and analyzed using Balance Clinic software (balance software for AMTI’s Accusway plus balance platform, version 2.02.01).

The measures will be the area of a 95% confidence ellipse of the COP excursion in the anterior-posterior and mediolateral directions and the mean velocity of the COP in two trials of 60 s, under six conditions: (1) orthostatic position on firm ground with open eyes (EO); (2) orthostatic position on firm ground with closed eyes (EC); (3) dual-task (DT): orthostatic position on firm ground with OE and performing two fluency tasks and counting backwards from 150 by subtracting 3’s (trial 1) and counting backwards from 180 by subtracting 3’s (trial 2); (4) orthostatic position on firm ground performing excursion in the anterior-posterior and mediolateral directions within the limit of stability; (5) orthostatic position on a foam pillow with OE; and (6) orthostatic position on a foam pillow with EC.

Postural control will be evaluated by the Mini Balance Evaluation Systems Test (Mini-BESTest), a scale that consists of 14 items that focus on dynamic balance, comprising four areas: anticipatory postural adjustments, postural responses, sensory orientation, and balance during walking. Each item is scored from zero to two; zero indicates that a person is unable to perform the task, while two means that the performance is normal. The maximum score is 28 [21].

Functional mobility will be evaluated by the Dynamic Gait Index (DGI), which measures dynamic balance, mobility, activities of daily living, and the risk of falls. This scale consists of eight tasks involving gait in different sensorial contexts, including level surfaces, changes in gait speed, horizontal and vertical movements of the head, walking over and around obstacles, turning on their own body axis, and up and down stairs. Each item is scored from zero to three; zero indicates gait with severe impairment, while three indicates normal gait. The maximum score is 24 points, and a score of 19 or less predicts risk for falls [22].

Gait will be assessed by Functional Gait Assessment (FGA), which consists of 10 items, seven of which include items that comprise the DGI, with additional tests: posterior gait, gait on the basis of reduced support, and gait with closed eyes. Each item is scored from zero to three, in which a score of zero indicates an inability to perform the task, while three is normal. According to the author, the best score is the maximum of 30 [23].

The analysis of the dual task will be evaluated by the Five Times Sit-to-Stand Test (SST) and 10-Meter Walk Test (10WT). The SST will be performed according to the description of Duncan, Leddy, and Earhart [24]. The individual will sit in the center chair, with back straight, feet parallel, and arms folded across the chest; they will be asked to get up and sit straight as soon as possible five times. A verbal command will be given to start and end the test, and during the test, they will be not given any form of incentive.

The 10WT will be realized in single and dual tasks. Participants will cross a distance of 10 m as described by Novaes, Miranda, and Dourado [25]. To eliminate the acceleration and deceleration components, the participants will be instructed to begin walking 1.2 m before the beginning of the course and to finish 1.2 m after the end of the course at usual speed. For both the SST and 10WM, in the single-task condition, it will record the time in seconds to complete the route. In the dual-task condition, it will measure the task execution time (in seconds) and the number of words spoken by the patients during the test.

Cognition will be evaluated by the Montreal Cognitive Scale (MoCA). The instrument assesses different cognitive domains, such as visuospatial and executive functions, namely, memory, attention, language, abstraction, delayed recall, and guidance. The total score of the scale is 30, and scores equal to or higher than 26 indicate normal performance [26].

Quality of life will be assessed by the Brazilian version of the Parkinson’s Disease Questionnaire (PDQ-39). It comprises 39 items divided into eight dimensions: mobility, activities of daily living, emotional well-being, stigma, social support, cognition, communication, and body of discomfort. Each item is scored from zero to four. The overall score ranges from zero (no problem) to 100 (maximum problem), but lower scores indicate better perception by the individual of their quality of life [27].

To evaluate the performance game, the score for each game will be compared in each session, comparing the first session (pretest) with the last session (posttest) and retention (30 days after).

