### Outcome measures

Individuals will be evaluated during the “on” period by two blinded, trained physical therapists. The evaluators will be blinded to the type of intervention that individuals will receive. Individuals will be oriented to not comment to the evaluators about any details of the intervention that they will receive. In compliance with the pharmacodynamics of levodopa (onset is 20 to 40 min and duration of effect is 2 to 4 h after medication), individuals will be evaluated in the period of 2 h after medication, according to Lipp et al. [20]. This is the time at which the individual had better engine performance related to the effect of levodopa.

Table 1 details the outcome measures that will be used to assess the treatment effects. All measurements will be taken at baseline (week 0), at the end of the intervention (week 7), and 30 days after the second evaluation (follow-up). For a month after the intervention, the individuals will be instructed to not begin any new physical activity in order to not interfere in the evaluation of the long-lasting effects of the intervention.

**Table 1 Tab1:** Summary of the outcome measures to be used in the study design

Outcome	Measurement tool
Primary outcomes	
Center of pressure and limits of stability	Posturography through the Balance Rehabilitation Unit
Secondary outcomes	
Postural control	Mini Balance Evaluation Systems Test
Functional mobility	Dynamic Gait Index and Functional Gait Assessment
Physical functioning	Five Times Sit-to-Stand Test and 10-Meter Walk Test
Cognition	Montreal Cognitive Scale
Quality of life	Brazilian version of the Parkinson’s Disease Questionnaire

Scales that will be used in the study protocol

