### Sample size

No formal sample size calculation will be performed for this feasibility study. We will follow the sample size recommendations for pilot randomized controlled trials [30], and we aimed to recruit 18 participants for each group (i.e., total sample size of 36) considering a dropout of 20%. This number of participants is deemed adequate to provide sufficient information on key feasibility issues such as recruitment and acceptability of the intervention.

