### Statistical analysis

The data analysis for the randomized controlled feasibility trial will be undertaken on an intention-to-treat basis. Demographic data will be presented to evaluate baseline comparability of the groups. Descriptive statistics will be used to characterize the groups at baseline and to present feasibility outcomes. Comparisons of the clinical outcomes between CG and EG will be performed to investigate the feasibility of this trial and to calculate estimates for likely effect sizes and 95% confidence intervals. Differences between the two groups will be presented as an unadjusted mean difference for continuous variables with their associated 95% confidence intervals; effect size will be calculated for paired *t*-test and *p* value with an alpha of 0.05, power of 0.8, and 0.5 correlations between baseline, at the end of the trial, and at follow-up. At the end of the study, data collection and statistical code will be publicly available, while maintaining the anonymity of the participants. All data will be analyzed using SPSS software version 22 (SPSS, Chicago, Illinois).

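### The limits-of-stability task in the primary clinical outcome is scored with sway area and mean velocity, which do not isolate how far the patient can lean

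*Protocol article*

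**What the plan says.** All of this is in the protocol article.

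- **Outcome measures, Table 1.** The primary row reads "Center of pressure and limits of stability", and the tool against it is "Posturography through the Balance Rehabilitation Unit".
- **Clinical outcomes, device.** "Static postural control and limits of stability (LOS) will be assessed using the AMTI Accugait Optimized™ force platform". COP is acquired at 100 Hz.
- **Clinical outcomes, first score.** "The measures will be the area of a 95% confidence ellipse of the COP excursion in the anterior-posterior and mediolateral directions".
- **Clinical outcomes, second score, with trial length and number of conditions.** This one is given as "the mean velocity of the COP in two trials of 60 s, under six conditions".
- **Clinical outcomes, condition 4.** "orthostatic position on firm ground performing excursion in the anterior-posterior and mediolateral directions within the limit of stability". This is the only condition with instructed leaning. The other five are standing with eyes open, eyes closed, a dual task, foam with eyes open and foam with eyes closed.
- **Statistical analysis.** "Differences between the two groups will be presented as an unadjusted mean difference for continuous variables with their associated 95% confidence intervals". Nothing says that the six conditions are averaged or combined.

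No maximum excursion, directional reach or limits-of-stability area is named. No direction of benefit is given for ellipse area or velocity in any condition, although the same section gives one for PDQ-39.

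**The concern.** Limits of stability are about how far a person can move the COP without losing balance. A 95% confidence ellipse is built from the variance of every sample in the trial, so in a leaning task it mixes how far the patient went with where the patient spent the time. Mean velocity is path length over time, so it mixes distance with pace. Two patients with the same limits can therefore get different scores, and a patient with smaller limits can score higher than one with larger limits.

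The reading of area also changes between conditions. In quiet standing a smaller ellipse is normally taken as better control; in condition 4 a larger one is what a gain in limits would produce. The article does not say so.

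What is at stake is the estimate passed on. The Statistical analysis section uses the clinical comparisons to estimate likely effect sizes, and the Discussion says that the results will size a larger trial. The games in Table 3 demand fast reactions and multidirectional weight shifting, so the arms could plausibly come to differ in how they lean without differing in how far they can lean.

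**Working it through.** The plan gives no figure to reproduce. The check asks how the two stated scores behave in a 60 s, 100 Hz leaning task.

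**Inputs from the article:** 60 s trials, 100 Hz, 95% ellipse area, mean COP velocity, leaning front-back and side to side.

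**Inputs assumed:** the lean amplitudes, the path shape, the time split and the cycle times.

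**Ellipse area.** Area = π × χ²(0.95, 2 df) × √det(covariance), with χ²(0.95, 2 df) = 5.991, so the constant is π × 5.991 = 18.82.

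*Path 1: holds at the limit.* Assume limits of ±A = 6 cm front-back and ±M = 8 cm side to side, half the trial on each axis, constant-speed leaning, and a fraction h of the time held at the limit. On the active axis the mean square is (1 − h)A²/3 + hA². Halving for the time on that axis gives a variance of A²(1 + 2h)/6, and likewise for M. The axes are uncorrelated, so

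Area = 18.82 × (A × M / 6) × (1 + 2h) = 18.82 × 8 × (1 + 2h).

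| Case | Multiplier | Formula (cm²) | Simulated path (cm²) |
|---|---|---|---|
| h = 0 | 1.0 | 150.6 | 150.6 |
| h = 0.2 | 1.4 | 210.8 | 210.9 |
| h = 0.4 | 1.8 | 271.0 | 271.1 |
| h = 0.6 | 2.2 | 331.3 | 331.3 |
| h = 0, limits × 1.2 | 1.44 | 216.8 | 216.9 |

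A 20% hold adds 40% with identical limits; a true 20% gain in limits adds 44%. The hold that exactly mimics that gain solves 1 + 2h = 1.44, so h = 0.22. Ranking can reverse: limits 20% smaller with a 60% hold give 0.64 × 331.3 = 212 cm², above the 150.6 cm² of the larger limits with no hold.

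*Path 2: rests at the centre.* This uses different assumptions: 5 cm and 6 cm amplitudes, smooth half-sine leans in four directions, a 12 s cycle, and a fraction d of the time at centre. Here Area = 18.82 × (A × M / 4) × (1 − d) = 141.2 × (1 − d). Simulated values agree with this to within 0.1 cm²:

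- d = 0: 141.2 cm²
- d = 0.2 (base): 113.0 cm²
- d = 0.5: 70.6 cm²
- lean 20% further, d = 0.2: 162.7 cm² (+44%)
- lean 20% further, d = 0.5: 101.7 cm², below the base case although the reach is larger

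The area enclosed by the four end points, 2 × 5 × 6 = 60 cm², is the same in the first three lines.

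**Mean velocity.** On path 2 one cycle covers 4 × (5 + 6) = 44 cm.

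- 12 s cycle: 44/12 = 3.67 cm/s
- 20 s cycle, same lean: 44/20 = 2.20 cm/s, with the ellipse unchanged at 113.0 cm²
- 12 s cycle, lean 20% further: 52.8/12 = 4.40 cm/s

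On path 1 with no hold, going from one to three lean cycles per axis raises velocity from 4 × (6 + 8)/60 = 0.93 to 2.80 cm/s, with the ellipse fixed at 150.6 cm².

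So dwell time moves the area, pace moves the velocity, and neither score alone recovers reach.

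**The case against.** A reader might infer that the two scores say nothing about leaning, or that benefit in condition 4 runs opposite to the other conditions on both scores. The documents do not support either. In condition 4 the ellipse is computed on instructed excursions and grows with the square of lean distance (1.2² = 1.44), so it is a confounded index of reach and not an unrelated one. The reversed direction applies to area precisely because area tracks lean. For velocity the desirable direction is unclear, not shown to be opposite.

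It is also tempting to say that faster leaning after game training would inflate the area. It would not: a change of pace alone leaves the ellipse unchanged. Pace affects velocity, dwell affects area, and nothing in the article shows that dwell would differ by arm.

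Other points on that side carry weight:

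- The amplitudes, paths and hold fractions are assumed. Instructions on pace and holds may stand in a fuller protocol or test manual, and standardising them would remove much of the distortion.
- No analysis combines the conditions, so a different sign in condition 4 corrupts nothing that is stated. It is a risk of misreading. Direction of benefit alone could be left to the analysis plan.
- This is a feasibility trial: "No formal sample size calculation will be performed for this feasibility study".
- Table 1 names a different instrument, so the scores in the text might not be the only ones intended.

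None of this supplies the missing variable. The article does fix the scores, and it fixes the same two for the leaning task as for standing. The instrument conflict is a second thing to settle and does not rescue the stated scores.

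**Conclusion.** The point holds in this form: limits of stability is part of the primary clinical outcome, and the scoring stated for it does not isolate how far the patient can lean. Ellipse area mixes reach with dwell, and mean velocity mainly reflects pace.

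On assumed paths, dwell alone can move the area by about as much as a real 20% gain in limits (40% against 44%) and can reverse the ranking of two patients. Those percentages illustrate the mechanism; the size in this trial depends on lean instructions that the article does not give. That area depends on dwell, and velocity on pace, follows from the definitions of the two scores.

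The change of direction for area between condition 4 and the standing conditions is an interpretation risk only, and it rests on the usual meaning of the tasks. The practical consequence is that an effect size for limits of stability taken from these scores would be hard to interpret when planning the larger trial.

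**What to change.** 1. For condition 4, name maximum COP excursion in each direction, or the area enclosed by the outermost COP path, as the limits-of-stability variable.
2. Keep ellipse area and mean velocity as the measures for conditions 1, 2, 3, 5 and 6, and at most as descriptive in condition 4.
3. State the direction of benefit by condition: for the new variable in condition 4 higher is better; for area and velocity in the standing conditions lower is better.
4. Say whether the excursion in condition 4 is meant to be maximal; the present wording leaves this open.
5. Reconcile the instrument for the primary outcome, given as the Balance Rehabilitation Unit in Table 1 and as the AMTI platform in Clinical outcomes.

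If the AMTI platform is the one used, the new variable comes from the same 100 Hz recordings, so the cost is wording and one derived variable, with no extra test or visit. If the other instrument is used, the authors should confirm that it yields an equivalent measure. The drawback is that maximum excursion rests on fewer samples and may be somewhat noisier; averaging the two trials limits this.

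### The dual-task word count in the sit-to-stand and 10-metre walk tests is tied to motor speed; the verbal component should be analysed as words per second

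*Protocol article*

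**What the plan says.** Under Clinical outcomes, the protocol article uses the SST and the 10WT to study dual-task performance. For both tests, "in the single-task condition, it will record the time in seconds to complete the route". The dual-task condition adds a verbal measure: "it will measure the task execution time (in seconds) and the number of words spoken by the patients during the test".

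Both tests end when a set amount of work is done. The 10WT covers 10 m, with a run-in and run-out, and patients are told "to finish 1.2 m after the end of the course at usual speed". The SST is five repetitions, and patients do it as fast as they can: "they will be asked to get up and sit straight as soon as possible five times".

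Table 1 (Outcome measures) lists "Five Times Sit-to-Stand Test and 10-Meter Walk Test" as secondary outcomes under physical functioning and gives cognition to the Montreal Cognitive Scale (MoCA).

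Under Statistical analysis, differences between the groups "will be presented as an unadjusted mean difference for continuous variables with their associated 95% confidence intervals". The article names no word rate and no adjustment of the word count for time.

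**The concern.** A count of events is comparable between patients, or between visits, only if the observation time is the same or is allowed for. Here the observation time is the motor result itself. A patient who walks or stands up faster has less time to speak, and so scores fewer words with the same verbal fluency. The count can fall because the patient has improved.

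Both arms train dual tasks (Tables 2 and 3), and the stated hypothesis is that both will improve. If both become faster, the count tends to drift down from pre to post in both arms. If one becomes faster than the other, the difference between arms shifts as well. The trial is meant to supply effect sizes for planning a larger study (Statistical analysis; Discussion), and an effect size taken from this count would mix two effects that can have opposite signs.

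The article's other dual task does not have this problem: the posturography trials last a fixed 60 s.

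**Working it through.** The article gives no figure that depends on the word count, so there is none to reproduce. The check follows from the definition of the measure.

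**Inputs.** From the article: a distance of 10 m, five stands, time in seconds, and words counted during the test. Assumed, because the article gives none: walking speeds, SST times and a speech rate of 0.8 words/s. The percentages in steps 1 and 2 do not depend on the speech rate.

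**Identity.** Words = rate × time. At constant rate, the relative change in words is t1/t0 − 1, which is the relative change in time.

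**Step 1, 10WT (time = 10 / speed), constant rate.**
- 1.0 to 1.1 m/s: 10.0 to 9.09 s; 9.09/10.0 − 1 = −9.1%.
- 1.0 to 1.2 m/s: 10.0 to 8.33 s; 8.33/10.0 − 1 = −16.7%. At 0.8 words/s this is 8.0 to 6.7 words.

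**Step 2, SST, constant rate.**
- 20 to 18 s: 18/20 − 1 = −10%.
- 20 to 16 s: 16/20 − 1 = −20%. At 0.8 words/s this is 16.0 to 12.8 words.

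**Step 3, a true verbal gain.** If the rate rises by 10% and the time falls by 20%, words change by 1.10 × 0.80 − 1 = −12%. A real improvement in both components appears as a lower count. To keep the count level with 20% less time, the rate would have to rise by 1/0.80 − 1 = 25%.

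**Step 4, difference between arms.** Only the difference in speed gain matters here. Suppose one arm goes from 1.0 to 1.10 m/s and the other from 1.0 to 1.15 m/s. The times become 9.09 and 8.70 s, and the counts change by −9.1% and −13.0%, a gap of about 4 percentage points. At 0.8 words/s the counts are 7.27 and 6.96, a gap of about 0.3 words. If both arms gain the same speed from the same baseline at the same word rate, the gap is zero.

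**Step 5, with the rate as the measure.** Count divided by time changes by 0% in every constant-rate case above. In step 3 it changes by 0.88/0.80 − 1 = +10%, which is the true verbal gain.

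**The case against.** The strongest reply is that the sentence under Clinical outcomes describes what is recorded, not what is analysed. Execution time and count are recorded together, so words per second can be formed at any point, and an analysis plan that is not shown may do so. The statistical paragraph is generic and does not mention words. All this is fair, and it limits the weight of the point: nothing irreversible has been fixed. It does not remove the point. The article names a raw count as the verbal measure and states only unadjusted mean differences for continuous variables. Taken together, these give a confounded score unless something is added.

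A reader might infer three stronger claims that the article does not support.

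- That a motor gain will be reported as a cognitive loss. No passage interprets the word count as cognition; MoCA has that role, and Table 1 places both tests under physical functioning. Misreading is a risk, not a stated plan.
- That the dual-task outcome as a whole moves in the wrong direction when treatment works. Execution time is measured in the same condition and moves in the right direction.
- That the between-arm comparison is biased by 9% to 20%. Those are within-patient changes at assumed values. The between-arm effect depends on how far the speed gains differ and may be small, as step 4 shows.

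It is also true that only the 10WT is done at a self-chosen pace. The SST is performed as fast as possible, but its duration still varies with motor ability, so the same identity applies. Finally, a shorter time gives fewer words only if the word rate does not rise enough to offset it, and dual-task training in both arms could raise that rate.

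**Conclusion.** The point holds in a limited form. As described, the verbal component of the dual-task SST and 10WT is mechanically tied to motor speed. At an unchanged word rate it falls by the same percentage as the execution time, about 9% to 20% in the examples worked, and it can fall even when the word rate truly improves. This affects pre-post change in either arm directly, and the difference between arms only in so far as their speed gains differ.

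The sizes rest on assumed speeds, times and, for the counts in words, an assumed speech rate. The proportionality itself does not. Execution time, MoCA, the primary posturography outcome, the sample size and the feasibility criteria are not affected. Because the outcome is secondary in a feasibility trial, the priority is low to moderate.

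**What to change.** Define the verbal component of the dual-task SST and 10WT as words per second: each patient's word count divided by that patient's recorded execution time on the same test. Present it alongside execution time, so that a trade-off between speed and speech is visible, and report the raw count descriptively only. For the 10WT, state that words are counted over the same stretch that is timed, without the 1.2 m run-in and run-out, so that numerator and denominator match.

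Dual-task cost in time, (dual − single) / single, is an optional addition, since both times are already recorded.

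The cost is a sentence or two in the analysis section. No new data, visits or procedures are needed, provided words are counted over the timed stretch.
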